# “Together at school” - a school-based intervention program to promote socio-emotional skills and mental health in children: study protocol for a cluster randomized controlled trial

**DOI:** 10.1186/1471-2458-14-1042

**Published:** 2014-10-07

**Keywords:** Children, Intervention, Promotion, Mental health, Socio-emotional skills, Whole school approach

## Abstract

**Background:**

Schools provide a natural context to promote children’s mental health. However, there is a need for more evidence-based, high quality school intervention programs combined with an accurate evaluation of their general effectiveness and effectiveness of specific intervention methods. The aim of this paper is to present a study protocol of a cluster randomized controlled trial evaluating the “Together at School” intervention program. The intervention program is designed to promote social-emotional skills and mental health by utilizing whole-school approach and focuses on classroom curriculum, work environment of school staff, and parent-teacher collaboration methods.

**Methods/Design:**

The evaluation study examines the effects of the intervention on children’s socio-emotional skills and mental health in a cluster randomized controlled trial design with 1) an intervention group and 2) an active control group. Altogether 79 primary school participated at baseline. A multi-informant setting involves the children themselves, their parents, and teachers. The primary outcomes are measured using parent and teacher ratings of children’s socio-emotional skills and psychological problems measured by the Strengths and Difficulties Questionnaire and the Multisource Assessment of Social Competence Scale. Secondary outcomes for the children include emotional understanding, altruistic behavior, and executive functions (e.g. working memory, planning, and inhibition). Secondary outcomes for the teachers include ratings of e.g. school environment, teaching style and well-being. Secondary outcomes for both teachers and parents include e.g. emotional self-efficacy, child rearing practices, and teacher-parent collaboration. The data was collected at baseline (autumn 2013), 6 months after baseline, and will be collected also 18 months after baseline from the same participants.

**Discussion:**

This study protocol outlines a trial which aims to add to the current state of intervention programs by presenting and studying a contextually developed and carefully tested intervention program which is tailored to fit a national school system. Identification of effective intervention elements to promote children’s mental health in early school years is crucial for optimal later development.

**Trial registration:**

ClinicalTrials.gov register: NCT02178332.

**Electronic supplementary material:**

The online version of this article (doi:10.1186/1471-2458-14-1042) contains supplementary material, which is available to authorized users.

## Background

There is a large body of research linking socio-emotional skills with a range of positive outcomes: children who have good socio-emotional skills tend to have better mental health, more friends, and perform better in school [1–3]. Thus, interventions based on socio-emotional learning (SEL) aiming to foster children’s social interaction skills and management of emotions, have been recommended as an important way to promote children’s mental health [1, 3–6].

Schools can be seen as key environments for the promotion of children’s mental health as they have existing school curricula, structures, policies, and resources [3, 6, 7]. The school-based programs are also able to reach a large number of children from different family backgrounds. Furthermore, the school context represents a natural and interactive set of environments comprising both direct (e.g. family, peers, class, school) and more distal (e.g. cultural, political) settings [3, 8].

Several reviews have reported that school- interventions can have positive effects on children’s mental health [3, 9]. Yet, meta-analyses of school-interventions have shown that the effect sizes have ranged from small to moderate in statistical terms indicating modest change in real life [4, 9]. Even though school interventions can be an important and cost-effective way of promoting children’s mental health, the high variability in their effectiveness poses unanswered questions.

Meta-analyses and systematic reviews have identified several components for effective interventions [1, 4, 9–12]. These components include for example placing emphasis on having a positive and holistic approach, in which the whole school targeted. Such effective interventions typically integrate the teaching of socio-emotional skills into a classroom curriculum, teach social skills using multimodal activities, and consider daily teacher-student interactions and practices. Further, such effective interventions typically consider family involvement and the role of leadership. Finally, high quality implementation (e.g. well defined goals and manualized guidelines), intervention beginning at the young age, and lengthy duration (at least 9 to 12 months) have been reported as key features of effective implementations.

The Finnish Ministry of Health and Social Affairs acknowledged the need for a program enhancing children’s socio-emotional skills in schools and initiated the development of a school-based intervention in 2003. However, it was not clear whether school interventions designed and implemented in other countries would be suitable for the Finnish school system and curriculum as such. Thus, the developers of the present intervention program studied the most well-known interventions and programs at the time (e.g. Good Behavior Game, Incredible Years, Lions’ Quest, Second Step, Responsive Classroom, Paths, Zippy’s Friends) along with the related effectiveness research. This process led to the development of the Together at school intervention program. It is a carefully developed and tested intervention program which combines unique elements developed especially to fit the Finnish school system and components that have been found to be effective in other school-based intervention programs. The intervention program aims to promote social-emotional skills and mental health in a whole school context, and consists of (a) a detailed manual, (b) training of intervention elements, and (c) regular school visits by the instructors.

The intervention program Together at school will be evaluated in a cluster randomized trial (RCT). The aim of the trial is to compare the Together at School intervention group with the control group to evaluate the effectiveness of the intervention program in a whole school context. The control group school teachers participated in two general lectures regarding socio-emotional skills in child development. The aims of the evaluation study are to: 1) Evaluate whether the newly developed whole school intervention program improves mental health and social skills among primary school children. 2) To examine the influence of the intervention program on school environment (e.g. teaching style, collaboration with parents) and children’s emotional-cognitive processes (e.g. emotional understanding, executive functions), and to test whether these secondary outcomes mediate the effectiveness of the intervention. 3) To examine the role of potential moderator factors influencing the effectiveness of the intervention, such as children’s initially poor executive functioning and low socio-economic status. 4) To evaluate certain feasibility aspects (e.g. recruitment attainment, drop-outs, data collection agreements) of the large scale implementation. The aim of this paper is to describe a study protocol of a cluster randomized controlled trial.

## Methods

### Study design

The study is an ongoing cluster randomized controlled trial (RCT) with two arms. Eligible schools were randomly allocated either to an intervention or a control group. Data has been collected at baseline, 6 months after baseline, and will be collected also 18 months after baseline from the same participants (children and their parents, teachers and the principals). Figure 1 outlines the participant flow and Table 1 outlines the data collection and intervention program timeline. Each school will participate in the study for two academic years from spring 2013 to spring 2015.

**Figure 1 Fig1:**
[figure not shown]
**Flow chart of participants.**

**Table 1 Tab1:** **Data collection and intervention program timeline**

	Baseline period (T_0_)									Post-intervention period (T_1_)							Post (T_2_)
	2013									2014							2015
	Mar	Apr	May	June-July	Aug	Sept	Oct	Nov	Dec	Jan	Feb	Mar	Apr	May	June-July	Spet-Dec	Mar-June
**Measuring points and informants**																	
	Teacher Principal	Teacher					Child_S_	Child_T_	Parent Dosage		Principal Teacher	Child_T_	Child_S_	Parent		Dosage	ALL
**Intervention schools**																	
Teachers with children					Training and school visit: *Circle Time, Home-School Cooperation*												
							Training and school visit: *Do It by Myself, We Talk Moment*										
										Training and school visit: *Do It Together*							
Principals with staff	Training and school visit: *Planning, placing and organizing Together at School procedures*																
						Training and school visit: *Staff Meeting*											
								Training and school visit: *Service Station*									
											Training and school visit: *Toolkit Session*						
**Control schools**																	
Principals and teachers								Lecture 1				Lecture 2					

*Note.* Teacher/Principal = Questionnaires about teaching and school environment, Child_S_ = Children’s computer based assessment, Child_T_ = Teacher assessment of children’s socio-emotional skills and academic skills, Parent = Questionnaires for parents about their children’s socio-emotional skills and home-school collaboration, Dosage = Intervention protocols for teachers and principals specifying the amount and content for the intervention methods and tools used, ALL = includes all measurements (i.e., Teacher, Principal, Child_S_, Child_T_, Parent, and Dosage).

### Ethics, data protection, and funding

The Ethical Committee of the National Institute for Health and Welfare (NIHW) in Helsinki, Finland has approved the trial study protocol. The trial has also been registered in the ClinicalTrials.gov registry (NCT02178322). All participants have been informed about the aim of the study and the related study procedure prior to their participation. An informed consent (children and parents) or agreement (teachers and principals) was required for active participation in the study. School and the class level data were collected with no possibility to distinguish the properties of individuals. The confidentiality of the participants is protected by using an encryption key for personal details in the data. The key is stored separately. Furthermore, all data are treated and implemented according to national data security laws. The trial (RCT) is funded by the Finnish Ministry of Education and Culture, the National Institute for Health and Welfare and the town of Ylöjärvi, which have also funded the development of the intervention program.

### Sample size

Power analyses were conducted to estimate the required sample size. The starting point for calculations was a multilevel model comprising two levels: school and pupil. It was assumed that 2-5 classes (typically 2-3) would participate per school, one class containing 20 pupils, the recruitment rate being 70% and attrition 10% during the follow-up. Calculations based on these assumptions resulted in a total of 25 (2*20*0.7*0.9) to 63 (5*20*0.7*0.9) children per school. The intra-cluster correlation coefficient (ICC) between schools for the primary outcome measure (SDQ total difficulties score) was assumed to be 0.15 [13] and the effect size between the intervention and control groups was expected to be a) 0.25 or b) 0.3. This is in line with corresponding research where the effect size has been found to vary between small and moderate [4, 9]. In a two level design using a significance level of 0.05 and requiring 80% power a sample size of a) 2400-5355 children (i.e. 96-85 schools) or b) 1675-3780 children (i.e. 67-60 schools) is required. Based on these calculations we decided to recruit 100 schools into the study. Sample size calculations were undertaken using Optimal Design Software [14].

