### Intervention

A synopsis including brief descriptions of the intervention methods and tools is outlined in Additional file 1. The methods and tools can be divided into three groups: class methods for the children carried out by the teachers, work environment methods for the school staff carried out by the principal and the staff, and teacher-parent collaboration methods carried out by the teachers. The class methods include: Circle time, Do it Myself -lesson and Do it Together -lesson, and individual discussion between the teacher and the child and material for the starting of the school year. The work environment methods are: Planning of Collaborative Time, Staff Meeting, Service Station, and Toolkit Session which are also designed to ameliorate and strengthen school development. The methods designed for teacher-parent collaboration are: materials for meeting the parents individually and as a group (Parents Evening). All methods and tools are described in a detailed intervention program Together at School manual (258 pages). The manual includes methods, tools and instructions for the teaching staff regarding pupil tutoring, teacher- parent collaboration, and working together as a staff. The intervention group teachers receive the manual during their training period and the control schools will receive the same manual after the last measuring point (T_2_ in spring 2015).

The teachers of the control schools were offered two lectures on socio-emotional skills (2 × 3 hours, altogether 6 hours). The first lecture was held in November 2013 and the second in March 2014 as described in Table 1.

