### Measures

The study was designed to evaluate children’s socio-emotional skills and mental health as primary outcomes, and related underlying mechanisms (i.e. emotional understanding, altruistic behavior, and executive functions) along with school and family related factors as secondary outcomes.

Also background information was collected from the teachers (regarding their own class and their professional background information), the principal (regarding their own class and/or professional and school background information), and parents (regarding family background information). Apart from the background information, a description of all measures used in the data collection is reported in Table 2.

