### Primary outcomes

The children’s *mental health* was measured with the four subscales of the Strengths and Difficulties Questionnaire (SDQ) assessing various psychological problems, such as conduct disorder, hyperactivity, peer relations, and emotional problems with the teachers and parents as raters [17–19]. The Finnish version of SDQ has shown adequate psychometric properties [20–22]. *Socio-emotional skills* were measured with one of the SDQ subscales measuring prosocial behavior and the Multisource Assessment of Social Competence Scale (MASCS) both rated by the parents and the teacher. The MASCS is an instrument designed to measure social competence in the Finnish elementary school context [23] and is partly based on the School Social Behavior Scale (SSBS) created by Merrell and Gimpel [24] for teachers to assess social behavior.

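### The sample size rests on one primary outcome, SDQ total difficulties, but the primary outcome lists name several other scores from two informants; the two must be reconciled.

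*Protocol article*

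**What the plan says.** The Sample size section speaks of one measure, "the primary outcome measure (SDQ total difficulties score", with a school-level ICC of 0.15, a standardised effect of 0.25 or 0.30, a 0.05 level and 80% power. It requires 96 to 85 schools at 0.25 or 67 to 60 schools at 0.30, for 25 to 63 children per school. It does not say whose rating or which follow-up is meant.

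Other sections use the plural. The Abstract says "The primary outcomes are measured using parent and teacher ratings" and names both the SDQ and MASCS. Measures gives "socio-emotional skills and mental health as primary outcomes". Under Primary outcomes, mental health "was measured with the four subscales of the Strengths and Difficulties Questionnaire (SDQ"), by teachers and parents, and socio-emotional skills use "one of the SDQ subscales measuring prosocial behavior and the Multisource Assessment of Social Competence Scale (MASCS) both rated by the parents and the teacher". Table 2 marks teacher and parent as informants for every primary row. Neither Table 2 nor the Primary outcomes section mentions the total difficulties score. They also disagree on peer relations, which Table 2 puts under socio-emotional skills and the Primary outcomes section puts under mental health.

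On timing, Study design says "Data has been collected at baseline, 6 months after baseline, and will be collected also 18 months after baseline". Neither follow-up is called primary. The Plan of statistical methods gives model types and adjustment factors but does not say which score, informant or follow-up carries the main conclusion.

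**The concern.** The 5% error rate and 80% power belong to one test of one score. A reader who goes from the Sample size section to the outcome lists cannot tell which test that is. The score it names is not among the listed primary outcomes, and its informant and time point are open. A result on any listed score could then be presented as primary, although the power calculation was done for a different one.

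The choice of informant matters separately. The programme includes "class methods for the children carried out by the teachers", and intervention teachers were trained for it, so they know their arm and also rate the primary outcomes. That is a question of bias, not multiplicity, but it is a reason to fix the informant in advance. The T1 data had already been collected when the article appeared, so the choice was still open with some follow-up data in existence.

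**Working it through.** **1. Reproduce the stated sizes as one test.** Inputs from Sample size: ICC ρ = 0.15, effect d = 0.25 or 0.30, n = 25 or 63 children per school, α = 0.05 (taken as two-sided, since sidedness is not stated), 80% power. For J schools in two equal arms,

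λ = d / √[4(ρ + (1 − ρ)/n) / J],

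and power comes from the noncentral t distribution with J − 2 degrees of freedom.

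- d = 0.25, n = 25, J = 96: ρ + (1 − ρ)/n = 0.15 + 0.85/25 = 0.184; λ = 0.25/√(4 × 0.184/96) = 2.855; power 80.7%.
- d = 0.25, n = 63, J = 85: λ = 2.850; power 80.4%.
- d = 0.30, n = 25, J = 67: λ = 2.862; power 80.5%.
- d = 0.30, n = 63, J = 60: λ = 2.874; power 80.7%.

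The smallest J reaching 80% is 95, 85, 67 and 60, against the stated 96, 85, 67 and 60. The arithmetic is sound, and it is for a single test.

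**2. Count the declared primaries.** The smaller count is three scores (one SDQ problem score, SDQ prosocial, MASCS) by two informants = 6 tests at one time point. Taking the four problem subscales separately gives 6 scores × 2 informants = 12.

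**3. False-positive chance if each test is at 0.05 and any one counts as success.** Under independence this is 1 − 0.95^k. With a common correlation r between the test statistics it follows by numerical integration. The document gives no correlations, so the values of r are assumptions.

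| Tests (k) | r = 0 | r = 0.5 | r = 0.7 |
|---|---|---|---|
| 6 | 26.5% | 20.7% | 16.4% |
| 12 | 46.0% | 31.9% | 23.2% |

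Twelve tests is also what three scores by two informants would give if both follow-ups counted.

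**4. Power if several primaries are kept and corrected.** Drop-out schools gives 79 schools. Children per school is an assumption: 3990 consented children × 0.9 retained / 79 = 45.5, and 44 is used here (45 gives the same whole percentages). At d = 0.25, λ = 0.25/√[4(0.15 + 0.85/44)/79] = 2.700; at d = 0.30, λ = 3.240. No covariate adjustment is assumed.

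| Level for each test | d = 0.25 | d = 0.30 |
|---|---|---|
| 0.05 (one test) | 76% | 89% |
| 0.025 (first Holm step, two tests) | 66% | 83% |
| 0.0125 (Bonferroni, four tests) | 56% | 75% |

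Four tests here means SDQ total and MASCS by two informants.

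**The case against.** The strongest objection is that hierarchy and multiplicity control are usually left to an analysis plan, which is not shown. That stands, so the absence of an adjustment is not part of this point. But which outcome is primary is a matter for the protocol, and this article answers it in two incompatible ways. One could read the four subscales as shorthand for a total, or SDQ total as the one primary picked for sizing. The text says neither.

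A reader might also infer that the trial declares both follow-ups primary, or that success on any one of 12 to 24 tests would count, so that the error rate is in fact far above 5%. The document does not support this. It collects the measures at two follow-ups without ranking them, and it states no success rule. The error rates above are conditional on a rule that the article does not contain.

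Three further objections hold in part:

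- The power loss is milder at effect 0.30. The 76% starting point reflects 79 schools rather than the planned 100, not multiplicity.
- Adjustment for baseline SDQ is planned and would raise power. If it explained 25% of the variance at both levels (an assumption), the fall at effect 0.25 would be from 87% to 71%.
- Preferring parent ratings is not a clean solution. Parents received a letter about the programme and are themselves reached by its teacher-parent methods, so they are not shown to be blinded. Nor is T2 the only follow-up after training: training ended in March 2014, and Table 1 puts the T1 parent questionnaire in May 2014.

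**Conclusion.** The contradiction is real and lies within the article. One score is sized as the primary outcome, a different and longer list is declared primary, and the sized score is missing from that list. The stated sizes are correct for SDQ total difficulties as a single test, so the 5% and 80% would apply to a defined claim once informant and time point are fixed. As written, these are not fixed.

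At stake is a false-positive chance of roughly 16% to 26% for six tests if any one sufficed, and more with the longer counts. If the primaries are kept and corrected over four tests, the loss of power is about 20 percentage points at effect 0.25 and 14 at 0.30. These figures rest on the test counts, the assumed correlations of 0 to 0.7, 44 children per school and no covariate adjustment. The contradiction rests on none of them. It would be too strong to say that the trial's error rate is known to be inflated, or that a result seen only in teacher ratings would be false.

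**What to change.** Before the T2 data are opened, bring the Abstract, Measures, Table 2, Primary outcomes and Sample size sections into line:

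- Name SDQ total difficulties as the one primary outcome, with one stated informant and one stated time point.
- Make the SDQ subscales, SDQ prosocial and MASCS secondary, together with the SDQ total from the other informant and at the other follow-up.
- If both informants must stay primary, use Holm across the two and restate the power. Without covariate adjustment, the first step at 0.025 has 66% power at effect 0.25 and 83% at 0.30.

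Parent rating is a reasonable choice because teachers deliver the class methods and know their arm, but the text should acknowledge that parents are not shown to be blinded either. T1 or T2 is for the investigators to choose and justify. If they choose T1, they should say whether any comparison by arm had been seen before the choice was made.

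The cost is wording in the analysis plan and a registry update. Several outcomes lose primary status. No new data are needed, and the original sizing stands if a single primary is kept.
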